**Outcomes:**

Baseline measurements and post-TPS evaluation of the ADHD symptoms and executive functions will also be conducted on all participants. The 1- and 3-month follow-up periods will be used to assess the long-term sustainability of the TPS intervention. For statistical analysis, ANOVA with repeated measures will be used to analyze data. Missing data were managed by multiple imputations. The level of significance will be set to *p* < 0.05.

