## Hypotheses

### Primary hypothesis

Participants in the verum TPS group will have a 30% reduction in the Swanson, Nolan, and Pelham Rating Scale (SNAP IV score) (i.e., attention deficit, hyperactivity impulse, and oppositional defiance) after 2 weeks of TPS treatment compared with the sham TPS group and be maintained at the 1- and 3-month follow-ups.

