### Sample size

To the best of our knowledge, there is no interventional study evaluating the efficacy of TPS on ADHD. Based on our previous open-label pilot RCT (39) evaluating TPS in adults with major depressive disorder that showed a large effect size (d = 0.91), we hypothesize a large effect of TPS in this study. We used G^*^power version 3.1.9.4 to calculate the target sample size. With a statistical power of 95% and a statistical significance level of 0.05 to detect a medium between-groups effect size (d) of 0.91 with four measurement time points, each group will require 15 subjects. A total sample of 30 is required in this trial. The attrition rate in our pilot MDD trial was 0%. We expect that the attrition rate in this ADHD trial would be < 5%. Subjects dropping out of the 2-week intervention period will be replaced by another enrolled subject in this pilot study.

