### Statistical analyses

All statistical analyses will be performed using the statistical software R for Windows (R version 4.1.0). Means and standard deviations (SD) for the continuous variables will be presented, while numbers and percentages for the categorical variables will be shown. A *p*-value of < 0.05 is considered statistically significant. Sociodemographic differences between the TPS group and the sham TPS group will be analyzed using the Chi-square test and *t*-test. If there are significant differences between sociodemographic factors, covariates will be considered confounding variables in the analyses. The normality of the primary outcome (SNAP-IV) scores will be tested by the Shapiro–Wilk test for each combination of factor levels (group and time). *T*-test will be used to test the baseline difference. A linear mixed model will be used to test the group (between-subject factor), time (within-subject factor), and group × time interaction effects of the SNAP-IV score between the TPS group and the sham TPS group. *Post-hoc* comparisons between groups and time points will be conducted using a *t*-test with Bonferroni correction. The normality of the secondary outcome scores will be tested by the Shapiro–Wilk test for each time point. For normally distributed outcomes, a linear mixed model will be used to determine whether the outcome scores are significantly different between the pre- and post-tests. For outcome scores that deviate grossly from normality, a non-parametric Friedman test will be used to test the mean difference. A Cohen's *d* effect size for each outcome will be calculated, where *d* = 0.2, 0.5, and 0.8 correspond to small, medium, and large effect sizes (54). Missing data will be managed by multiple imputations (55). For the neurological rs-fMRI data, a longitudinal voxel-based morphometry (VBM) will be used to examine whether TPS produces local changes in gray matter. Specifically, relative local increases and decreases between pre- and post-intervention scans will be compared within and between study groups. The diffusion MR data will be analyzed using the diffusion tensor model (56). Two standard diffusion indices will then be obtained: the apparent diffusion coefficient and the fractional anisotropy. Pre- and post-treatment DTI scans will permit the assessment of changes in axial diffusivity, with lower values being interpreted as the structural enhancement of white matter.

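### The primary hypothesis concerns verum against sham at T2, but the plan does not say which model effect decides it and compares the arms at T2 only by Bonferroni-corrected post-hoc t-tests

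*Protocol article*

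**What the plan says.** - **Primary hypothesis:** a 30% SNAP-IV reduction in the verum arm "after 2 weeks of TPS treatment compared with the sham TPS group and be maintained at the 1- and 3-month follow-ups". The comparison is between arms, first at T2 and then at T3 and T4.
- **Statistical analyses, model:** "A linear mixed model will be used to test the group (between-subject factor), time (within-subject factor), and group × time interaction effects" of the SNAP-IV score. No effect or contrast is singled out as decisive.
- **Statistical analyses, follow-up tests:** post-hoc "comparisons between groups and time points will be conducted using a" t-test with Bonferroni correction. The number of comparisons is not given. Baseline SNAP-IV has its own t-test but is not named as a covariate. Covariates enter only if sociodemographic factors differ between arms.
- **Abstract, Outcomes:** "ANOVA with repeated measures will be used to analyze data".
- **Sample size:** "With a statistical power of 95% and a statistical significance level of 0.05 to detect a medium between-groups effect size (d) of 0.91", and "with four measurement time points, each group will require 15 subjects".

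**The concern.** The three model effects do not answer the stated hypothesis equally well.

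- **Time** does not compare the arms.
- **Group** averages over all four visits, including the one before treatment, where randomisation makes the expected difference zero.
- **Group × time** rejects for any divergence of the arms over the four visits and does not say where it occurs.

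The comparison that the hypothesis puts first, verum against sham at T2, is reached only in the post-hoc step, at a fraction of 0.05 and without stated use of the baseline score. In a trial of 30 patients that is a material loss on the main question. Leaving the deciding effect unnamed also means that the reading of a mixed set of results is not fixed in advance.

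**Working it through.** **Inputs from the protocol article:** d = 0.91, n = 15 per arm, four visits, significance level 0.05.

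**Assumptions, not in the document:** two-sided testing; a constant within-patient correlation ρ of 0.3, 0.5 or 0.7; a Bonferroni family of 3 (arms compared at T2, T3, T4, since baseline has its own test) or 4 (all visits); complete data; no baseline difference in expectation. The sustained pattern is (0, 0.91, 0.91, 0.91) SD at T1 to T4. The decaying pattern is (0, 0.91, 0.6, 0.3) SD.

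**1. The plan's own figure.** A two-sample t-test at d = 0.91 needs 33 per arm for 95% power. With 15 per arm it has 67%. A repeated-measures between-arm test with f = 0.91/2 = 0.455 and noncentrality N·f²·4/(1 + 3ρ) gives N = 30 only at ρ of about 0.25: 30 × 0.207 × 4 / 1.75 = 14.2, power 95%. At ρ = 0.5 it needs N = 42. The article states no ρ, so 15 per arm does not follow from what it states. That formula also takes 0.91 as the difference averaged over all four visits, baseline included.

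**2. T2 t-test as planned.** Noncentrality 0.91 × √(15/2) = 2.49 on 28 df.

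| Level | Power |
|---|---|
| 0.05 (single test) | 67% |
| 0.05/3 | 49% |
| 0.05/4 | 44% |

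**3. T2 contrast adjusted for baseline, single test at 0.05.** The effect becomes 0.91/√(1 − ρ²), on 27 df.

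| ρ | Adjusted effect | Power |
|---|---|---|
| 0.3 | 0.954 | 71% |
| 0.5 | 1.051 | 79% |
| 0.7 | 1.274 | 92% |

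A simulation of 20,000 trials per scenario gives 70%, 78% and 91%.

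**4. Where the gain comes from (family of 4, ρ = 0.5).** Dropping the alpha split: 44% to 67%, 23 points. Adding the adjustment: 67% to 79%, 12 points.

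**5. Group effect.** Averaging in T1 gives (0 + 3 × 0.91)/4 = 0.68 SD. The noncentrality is (15/2) × 4 × 0.6825² / (1 + 3ρ), on F(1, 28).

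**6. Group × time effect.** The noncentrality is (15/2) × Σ(d_t − mean)² / (1 − ρ), on F(3, 84). The sum of squares is 0.621 if sustained and 0.459 if decaying.

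| Test | ρ = 0.3 | ρ = 0.5 | ρ = 0.7 |
|---|---|---|---|
| Group, sustained | 74% | 63% | 54% |
| Group × time, sustained | 54% | 71% | 91% |
| Group × time, decaying | 42% | 56% | 80% |
| Adjusted T2 contrast, either pattern | 71% | 79% | 92% |

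**The case against.** **The hypothesis is about a course over time.** It covers T2 and maintenance at T3 and T4, and group × time followed by corrected visit comparisons is a conventional, conservative way to test that. This stands in part. A reader might infer that the plan tests the wrong question or throws away most of its power, and the figures do not support that for the interaction. Under the sustained effect that the hypothesis states, it is 8 points below the adjusted contrast at ρ = 0.5 and about equal at 0.7. The clear shortfall is at ρ = 0.3, or if the effect fades, which the hypothesis does not assume. At ρ = 0.3 with a sustained effect, the group test (74%) even slightly exceeds the contrast (71%).

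**The loss depends on the Bonferroni family.** If it covered all 28 pairs of the 8 arm-by-visit cells, the T2 test would have only 20% power. The article does not describe such a family, and many of those pairs answer no question, so that figure should not be used. The loss at 3 or 4 comparisons remains.

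**Contrast, covariate and testing order are often left to the SAP.** That is true of details, but here the article fixes a procedure. An SAP that followed it would inherit the unnamed deciding effect and the divided alpha at T2.

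**The abstract.** A reader might infer that it names a rival primary analysis. It does not call its ANOVA primary. With complete data and constant correlation the two methods agree. Multiple imputation is stated in both places and attrition is expected below 5%. This is a wording inconsistency.

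**Reporting a time effect as the result.** The hypothesis specifies comparison with sham, so a time effect alone could not satisfy it. The document gives no ground to expect such reporting.

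**Conclusion.** The point holds in limited form. The article does not say which effect decides the primary hypothesis, and its only stated comparison of the arms at T2 is an alpha-divided t-test without stated baseline adjustment. Against one baseline-adjusted contrast on the same 30 patients, that t-test loses 22 to 43 points of power with 3 comparisons (71 − 49 to 92 − 49) and 27 to 48 with 4 (71 − 44 to 92 − 44). Dropping the alpha split and adjusting for baseline both contribute. The interaction test is a reasonable overall test at moderate to high correlation, but it does not locate the effect at T2.

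These sizes rest on d = 0.91 and on assumed sidedness, correlation and family size. None of the tests in the table reaches 95% power at correlations of 0.3 to 0.7, so the sample-size statement is a separate problem.

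**What to change.** In Statistical analyses:

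1. Name the verum–sham contrast in SNAP-IV at T2 from the mixed model, adjusted for baseline SNAP-IV, as the primary test at two-sided 0.05.
2. Test T3 and then T4 in that order, each at 0.05 and only if the previous test is significant. This matches the maintenance part of the hypothesis without dividing alpha across visits.
3. Treat the time effect and the overall group effect as descriptive.
4. Leave the three SNAP-IV factors in the role that Primary hypothesis and Primary outcome give them.

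In the abstract, replace the repeated-measures ANOVA by the mixed model.

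The cost is wording only, with no added patients or visits. The downside is that an effect appearing only at T3 or T4 could not be claimed as primary. The change does not bring power to the stated 95%.

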**Methods:**

This study proposes a double-blinded, randomized, sham-controlled trial including TPS as an intervention group and a sham TPS group. Both groups will be measured at baseline (T1), immediately after the intervention (T2), and at the 1-month (T3) and 3-month follow-ups (T4).

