### Secondary outcomes

#### Clinical Global Impression

The Clinical Global Impression (CGI)—severity and improvement scale (CGI-S and CGI-I) is generally used to assess illness severity and global improvement. CGI-S is a 7-point clinician rating scale based on observed and reported symptoms, behavior, and function in the past 7 days. CGI-I is a 7-point scale to assess whether the patient's ADHD condition has improved or worsened compared to the baseline. CGI-S and CGI-I will be used to supplement each other (47). These scales had been used in a double-blinded placebo-controlled RCT (48).

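### A per-visit normality test with no stated cut-off decides whether a secondary outcome gets a mixed model or a Friedman test, and the Friedman test has no verum–sham comparison

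*Protocol article*

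**What the plan says.** The protocol article, Statistical analyses, sets a two-step rule for the secondary outcomes. The first step is a test of the scores themselves: "The normality of the secondary outcome scores will be tested by the Shapiro–Wilk test for each time point". The second step chooses the method. One branch reads: "For normally distributed outcomes, a linear mixed model will be used to determine whether the outcome scores are significantly different between the pre- and post-tests". The other reads: "For outcome scores that deviate grossly from normality, a non-parametric Friedman test will be used to test the mean difference".

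The only significance threshold in that section is general: "A *p*-value of < 0.05 is considered statistically significant". The text does not say whether it applies to the Shapiro–Wilk test, what counts as gross deviation, what happens when visits disagree, or what happens to an outcome that is neither normal nor grossly non-normal.

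SNAP-IV, the primary outcome, is treated differently. Its normality is tested by group and time, and its linear mixed model with group, time and group × time is stated with no normality-dependent fallback.

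The secondary outcomes include CGI ("CGI-S is a 7-point clinician rating scale"), the Stroop test and ADHD RS-IV. The Secondary hypotheses section words the expected gains in ADHD symptoms and behaviour and in executive function as verum compared with sham, after treatment and at 1 and 3 months.

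**The concern.** A randomised sham-controlled trial earns its inference from the comparison between arms. Here the observed scores, plus an unspecified judgement, decide whether that comparison is made for a given secondary outcome. A mixed model can carry group × time; a Friedman test cannot. One outcome could be reported as a verum–sham contrast and a related one, such as the other ADHD RS-IV subscale, as a change over time that includes placebo response and natural course.

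The gate also looks at the wrong quantity. A mixed model assumes normal residuals given arm and visit, not normal raw scores. By contrast with the SNAP-IV wording, the secondary scores appear to be tested with both arms pooled, although that is an inference.

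**Working it through.** **Plan's own figure.** The article gives none for this step, so there is nothing to reproduce. The sample size is taken as stated.

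**Inputs from the article**
- Visits: 4 ("Both groups will be measured at baseline (T1), immediately after the intervention (T2), and at the 1-month (T3) and 3-month follow-ups (T4").
- Subjects: 30 ("each group will require 15 subjects. A total sample of 30 is required in this trial").
- Nominal level: 0.05, applied to Shapiro–Wilk by inference.

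**Assumptions**
- The switch is triggered by a small p-value at any one visit, with both arms pooled.
- CGI-S is a rounded normal on 1–7 with mean 4–5, SD 0.7–1.5 and between-visit correlation 0.6. The article gives no CGI-S mean or SD.

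**1. What the Friedman branch tests.** With n subjects, k visits and R_j the sum of within-subject ranks at visit j,

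Q = 12 / [n k (k + 1)] × Σ R_j² − 3 n (k + 1).

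For n = 30 and k = 4, 12/600 = 0.02 and 3 × 30 × 5 = 450, so Q = 0.02 Σ R_j² − 450. The arm label appears nowhere. Two extreme cases:
- All 30 subjects, in both arms, improve in the same perfect order. R_j = 30, 60, 90, 120 and Σ R_j² = 27,000, so Q = 540 − 450 = 90. That is the maximum, n(k − 1), with no difference between arms.
- The 15 verum subjects improve in perfect order and the 15 sham subjects worsen in reverse order. Each R_j = 15j + 15(5 − j) = 75 and Σ R_j² = 22,500, so Q = 450 − 450 = 0, with the arms moving in opposite directions.

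Running the test separately in each arm would still give no test of the difference between arms.

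**2. A truly normal outcome.** With independent visits, P(at least one p < 0.05 in four) = 1 − 0.95⁴ = 18.5%. Simulated with n = 30 (8,000 runs each):

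| Between-visit correlation | 0 | 0.3 | 0.5 | 0.7 | 0.8 | 0.9 |
|---|---|---|---|---|---|---|
| Flagged at some visit | 18.6% | 19.0% | 17.7% | 17.3% | 16.6% | 14.4% |

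This rate comes from the level and the number of looks, not from having 30 subjects. With only one pre and one post visit it would be 1 − 0.95² = 9.75%. At an illustrative trigger of p < 0.001, 1 − 0.999⁴ = 0.4%; simulation gives about 0.3–0.6%.

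**3. CGI-S** (4,000 runs per setting; ranges are over means 4, 4.5 and 5):

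| SD | Some visit, p < 0.05 | One given visit, p < 0.05 | Some visit, p < 0.001 |
|---|---|---|---|
| 0.7 | 100% | 100% | 99–100% |
| 0.9 | 100% | 98–100% | 69–78% |
| 1.0 | 100% | 92–98% | 45–53% |
| 1.2 | 99–100% | 76–90% | 16–20% |
| 1.5 | 91–100% | 47–84% | 3–11% |

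**4. Does the gate itself distort the error rate?** The two-stage rule was simulated with a valid between-arm fallback in place of Friedman. The settings were Shapiro–Wilk at four visits, n = 30, correlation 0.5, then a t-test at T2 if not flagged and Mann–Whitney if flagged. At a 0.05 trigger, type I error was 4.6% (normal), 4.9% and 4.8% (lognormal, sigma 0.4 and 0.6) and 4.9% (rounded CGI-S). Over both triggers it lay between 4.4% and 5.0%. With 4,000 runs the simulation standard error is √(0.05 × 0.95/4,000) = 0.34 percentage points, so no inflation is seen.

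**The case against.** The strongest objection is that the flagging rates belong to a rule the article does not state. It switches only outcomes that deviate grossly and never says that one p < 0.05 at one visit is enough. This stands: the rates illustrate one reading, and the stricter trigger changes them greatly. It does not rescue the plan, because it means the switch has no defined operating rule.

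A reader might go further and infer that the gate invalidates the reported p-values whatever test is used as the fallback. The article does not support that. No inflation appeared when the fallback was a valid between-arm test, so the harm lies in switching between analyses that answer different questions.

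It can also be said that if CGI-S is nearly always flagged, its method is in effect fixed. Under the 0.05 reading this is fair, but the method it is then fixed to has no group term.

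Two points of scope also stand. Only secondary outcomes are affected, and an article may leave the cut-off and residual checks to an analysis plan not shown. The rule itself, however, is stated here, with both branches named.

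Finally, the mixed-model sentence for secondary outcomes mentions only pre- and post-test differences. Reading it as the SNAP-IV model with group terms is charitable. CGI is also not named in any secondary hypothesis, although in a sham-controlled trial only the between-arm contrast bears on efficacy.

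**Conclusion.** The point holds for the secondary outcomes. As written, the data and an undefined judgement choose between a model that can estimate the verum–sham difference and a test that cannot. CGI-S is the outcome most exposed, since a 7-point rating is visibly discrete.

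The frequency cannot be fixed from the article. Between the two illustrative triggers, p < 0.05 and p < 0.001 at any visit, it runs from about 14–19% down to 0.3–0.6% for a truly normal outcome, and from 91–100% to 3–100% for CGI-S under the assumed distributions. The Friedman result needs no such assumption, because the statistic does not use the arm label. Neither type I error inflation from the gate nor any effect on the SNAP-IV analysis is shown.

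**What to change.** Delete the Shapiro–Wilk gate for secondary outcomes and name one between-group method per outcome, by type of scale, before unblinding:
- **ADHD RS-IV and the Stroop score:** the linear mixed model with group, visit and group × visit, as already stated for SNAP-IV, with the verum–sham contrasts at T2, T3 and T4 written out.
- **CGI-S:** an ordinal or rank-based verum–sham comparison.
- **Diagnostics:** check normality on model residuals after fitting, with one pre-stated sensitivity analysis that does not replace the named method.

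The cost is a few sentences in Statistical analyses and a little extra analysis. It needs no further subjects, visits or data.

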### Secondary hypotheses

Participants in the verum TPS group or the sham TPS group will have < 5% somatic discomfort during the 2-week TPS intervention on young adolescents with ADHD.Participants in the verum TPS group will have a 30% improvement in ADHD symptoms and behavior compared with the sham TPS group after 2 weeks of TPS treatment and be maintained at the 1- and 3-month follow-ups.Participants in the verum TPS group will have a 30% improvement in executive function after 2 weeks of TPS treatment compared with the sham TPS group and be maintained at the 1- and 3-month follow-ups.Participants in the verum TPS group will have a 30% improvement in both attention deficit and reduction in hyperactivity and impulsivity after 2 weeks of TPS treatment compared with the sham TPS group, and be maintained at the 1- and 3-month follow-ups.Participants in the verum TPS group will have more brain connectivity changes after 2 weeks of TPS compared with the sham TPS group and be maintained at the 1- and 3-month follow-ups.

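### The tests named for the secondary outcomes (ADHD RS-IV, Stroop, CGI) do not compare verum with sham, so improvement shared by both arms could be read as an effect of TPS

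*Protocol article*

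**What the plan says.** **Hypotheses.** Under Secondary hypotheses, the efficacy claims are set against sham. For the ADHD RS-IV domain the claim is "30% improvement in ADHD symptoms and behavior compared with the sham TPS group after 2 weeks of TPS treatment"; for the Stroop domain it is "30% improvement in executive function after 2 weeks of TPS treatment compared with the sham TPS group". Both are to persist at the 1- and 3-month follow-ups.

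**Analysis of the primary outcome.** The Statistical analyses section specifies a linear mixed model with group, time and "group × time interaction effects of the SNAP-IV score between the TPS group and the sham TPS group".

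**Analysis of the secondary outcomes.** The same paragraph then says that, for normally distributed secondary outcomes, "a linear mixed model will be used to determine whether the outcome scores are significantly different between the pre- and post-tests". For scores far from normal, "a non-parametric Friedman test will be used to test the mean difference". The choice rests on Shapiro-Wilk tests at each time point. No group or interaction term is named.

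**CGI-I.** The Clinical Global Impression section defines it as a rating of whether the patient's condition "has improved or worsened compared to the baseline".

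**Abstract.** It says only that "ANOVA with repeated measures will be used to analyze data", without naming a contrast.

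**The concern.** A sham arm allows one to subtract whatever happens to both groups: placebo response, regression to the mean, and practice on repeated tests. A pre-post test or a Friedman test leaves all of that in.

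Shared improvement is likely here. The screening section recruits subjects with a SNAP-IV mean above 2, so some regression to the mean should be expected on parent-rated symptom scales covering the same domains, such as the ADHD RS-IV. Practice on a repeated Stroop test is a plausible further source, although the protocol does not discuss it. The protocol itself warns, of the earlier TPS studies without a sham control, that placebo effects must be considered.

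If the plan is followed as worded, a significant secondary result could be reported as support for TPS when both arms improved equally.

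**Working it through.** **1. Which contrast goes with which outcome**

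| Outcome | Hypothesis | Contrast in Statistical analyses or Neuroimaging |
|---|---|---|
| SNAP-IV (primary) | verum vs sham | group, time, group × time |
| ADHD RS-IV, Stroop | verum vs sham | pre vs post, or Friedman |
| CGI-S, CGI-I | listed as secondary outcomes | pre vs post, or Friedman |
| Imaging | verum vs sham | between groups: dual regression for rs-fMRI; for VBM, "relative local increases and decreases between pre- and post-intervention scans will be compared within and between study groups" |

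The group factor is also missing from the secondary normality check. SNAP-IV normality is tested by group and time, secondary normality by time point only. The Bonferroni post-hoc comparisons between groups follow the SNAP-IV model and come before the secondary outcomes are introduced.

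**2. What each test can detect**

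Let both arms improve by δ (in SD units) after baseline, with no verum-sham difference and within-subject correlation ρ. The SD of the T1–T2 change is √(2(1 − ρ)).

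- Pre-post test on n subjects: noncentrality = δ√n / √(2(1 − ρ)). With δ = 0.5, ρ = 0.5 and n = 30 this is 0.5 × 5.48 / 1 = 2.74. For the verum arm alone (n = 15) it is 0.5 × 3.87 / 1 = 1.94. Neither is zero, although TPS has no effect.
- Between-arm test of change: the expected difference is δ − δ = 0, so the false-positive rate stays at the nominal 5% for any δ.
- Friedman test: it ranks the four visits within each subject. It therefore responds to δ and has no term for arm.

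**3. How often a test is significant with no verum-sham difference**

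Inputs from the protocol: 15 per arm, four visits, significance level 0.05. Assumed, because the protocol does not give them: δ, ρ, normal data, two-sided tests. There were 20,000 simulated trials per setting.

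| ρ | δ (SD) | Pre-post, all 30 | Pre-post, verum only | Friedman, all 30 | Friedman, verum only | Between-arm change |
|---|---|---|---|---|---|---|
| 0.5 | 0 | 4.9% | 5.1% | 4.8% | 4.8% | 5.0% |
| 0.5 | 0.3 | 35.7% | 19.4% | 26.9% | 14.4% | 5.1% |
| 0.5 | 0.5 | 75.7% | 44.4% | 66.2% | 34.1% | 4.9% |
| 0.5 | 0.8 | 98.9% | 82.2% | 98.1% | 74.1% | 4.9% |
| 0.7 | 0.3 | 53.4% | 28.8% | 43.1% | 21.4% | 5.1% |
| 0.7 | 0.5 | 92.8% | 63.8% | 88.1% | 53.9% | 4.8% |
| 0.7 | 0.8 | 100.0% | 96.0% | 100.0% | 93.1% | 4.7% |

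The protocol does not say whether the pre-post or Friedman test pools the arms or is run within verum, so both readings are shown. A separate simulation of 4,000 trials per setting (ρ = 0.5, δ = 0.5 and 0.8) found that a baseline-adjusted (ANCOVA) comparison of arms at T2 also stays at 5%.

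**4. CGI-I**

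CGI-I is itself a rating of change, so there is no T1 score and a pre-post contrast cannot be formed. A Friedman test over T2 to T4 could be computed, but it would ask only whether ratings drift after treatment, not whether the arms differ.

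**The case against.** The best counter-argument is that a linear mixed model can carry a group × time term. The protocol defines such a model for SNAP-IV a few lines earlier, and the article is condensed, so the secondary sentence may simply be loose. That is possible, but the text gives a different purpose for the secondary model. Nor does this reading rescue the Friedman branch, which cannot include arm. That branch is a realistic route with 15 per arm and 7-point CGI ratings.

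Other points on that side:

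- **No stated success rule.** The protocol does not say that a pre-post p-value below 0.05 counts as success, and a Cohen's d is promised for each outcome. This stands in part: a false claim could follow but is not certain. Cohen's d is an effect size, not a test, and its contrast is not stated for these outcomes.
- **Assumed inputs.** The improvements and correlations in the simulation are not from the protocol. This stands. At 0.3 SD and correlation 0.5 the pooled pre-post rate falls to 36%. The choice of contrast is wrong whatever the values.
- **Shapiro-Wilk on raw scores.** At a single visit, raw scores differ from the marginal residuals of a model with group and visit only by a constant, unless the arm means differ. This largely stands, so the normality point is minor.
- **Secondary outcomes in a pilot.** True, and the primary analysis is sound. But the correction is cheap, and without it no clinical or cognitive secondary result can be attributed to TPS.

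**Conclusion.** The plan is wrong as written for the outcomes under its Secondary outcomes heading: CGI, Stroop and ADHD RS-IV. The stated pre-post contrast does not test the verum-sham hypotheses, the Friedman fallback cannot, and the pre-post test cannot be formed for CGI-I. This is not detail left to the SAP, because the protocol states the test and the test does not match its own hypotheses.

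With no verum-sham difference and a common improvement of 0.3 to 0.8 SD, the stated tests are significant in 27% to nearly 100% of trials when arms are pooled, and in 14% to 96% within verum alone. A between-arm contrast gives about 5% throughout. These rates assume correlations of 0.5 or 0.7 and normal data; the mismatch itself rests on no assumption. The SNAP-IV analysis and the imaging comparisons are outside this point.

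**What to change.** In Statistical analyses, replace the two sentences on testing the secondary outcomes with the following:

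- **ADHD RS-IV, Stroop and CGI-S:** the same linear mixed model as SNAP-IV, with group, time and group × time. The reported result is the baseline-adjusted verum-sham difference at T2, T3 and T4.
- **CGI-I:** a between-arm comparison at T2, T3 and T4, by Wilcoxon rank-sum test or an ordinal model.
- **Non-normal outcomes:** drop the Friedman test and use a between-arm method, such as rank ANCOVA or a permutation test of the baseline-adjusted difference.
- **Normality:** check it on model residuals.

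The Abstract should name the same model. Other between-arm methods would also serve; what matters is that each secondary test contains the arm comparison. The cost is analysis wording only, with no new data, visits or subjects.
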